### Sample

To calculate the sample size, the QuestionPro software (QuestionPro Inc) was used [32]. It consists of software that, among other functions, incorporates a sample calculator for research.

Based on breast cancer morbidity data in the province of Almeria for 2022, published by the National Institute of Statistics [33], the calculation assumed a moderate effect size of 0.5, based on prior research on exercise interventions in similar populations. To ensure sufficient sensitivity to detect meaningful differences, the significance level (α) was set at .05 (2-tailed), and the study power (1–β) was set at 80%. Considering these assumptions, an initial sample size of 280 participants was determined. However, recognizing the potential for participant dropout, which is common in exercise-based trials, we accounted for an estimated attrition rate of 15%. To compensate for this and maintain statistical power, the final sample size was adjusted to 325 participants.

This approach ensures that the study is adequately powered to detect significant differences between the intervention and control groups for the primary outcomes. If further specifics or expanded parameters are required, we are happy to provide additional details. This explanation aims to address editorial concerns and clarify the robustness of our calculation methodology.

In the beginning, an attempt will be made to recruit the estimated size of participants; if this cannot be done, a smaller sample size will be used, assuming a decrease in the confidence level of the results.

### Randomization

All participants have the same probability of belonging to either group. Assignments will be randomized with a 1:1 ratio using the OxMaR software (OxMaR Inc) in its Spanish version [34].

### Measuring Tools for Evaluation

#### Disability of the Arm, Shoulder, and Hand Questionnaire

Self-administered and validated questionnaire in Spanish, the original questionnaire was first published in 1996 [35]. This measuring instrument assesses the impact of processes occurring in the upper limb. This questionnaire consists of 30 items and 2 optional modules. The score obtained is transformed to a scale from 0 to 100, where higher scores show a worse result. It shows a high internal consistency (Cronbach α=0.96) [36].

#### Brief Pain Questionnaire

This questionnaire is a pain assessment instrument used to measure pain intensity and its impact on the patient’s daily life; the original questionnaire was developed at McGill University in 1971, with an internal consistency of 0.7 [37]. The questionnaire used in the study was validated in Spanish in patients with neoplastic pain. It consists of 11 items on a Likert-type scale from 0 to 10 (where 0=no pain and 10=worst possible pain) and 15 additional items that assess the impact of treatment on pain relief. It presents a high internal consistency, with Cronbach α being higher than 0.7 in all dimensions (0.89 for pain intensity and 0.87 for impact on daily life) [38].

#### Muscle Assessment

Muscle strength will be assessed using a 1 maximum repetition (MR) protocol for the chest press in the horizontal plane and the leg press, as this is the most commonly used muscle assessment test in similar studies, according to the meta-analysis by Hasenoehrl et al [39]. One RM is defined as the maximum weight at which only 1 repetition can be performed [40].

For the evaluation, we will start with an initial warm-up series with 6 repetitions, the initial weight will be 2.5 kg and 18 kg for the upper and lower limbs, respectively. According to the perceived effort of each participant, we will start with an approximate weight for the one RM test, until it increases according to tolerance to find out the 1 RM weight of each participant. This is the strategy followed by Brown and Schmitz [41]. The assessment of the upper limb will be performed unilaterally in order to objectively evaluate the difference between the affected and healthy upper limb, as was done by Hagstrom et al [42]. Thus, we will start with 1.25 kg for each upper limb.

#### EORTC-QLQ-C30 Quality of Life Questionnaire

A questionnaire was created by the European Organization for Research and Treatment of Cancer (EORTC) to assess the quality of life in patients with cancer. The organization provides the questionnaire translated into several languages, including Spanish. It consists of 30 Likert-type questions that assess various aspects of quality of life, including the ability to perform activities, symptom control, general perception of health, and other relevant aspects such as difficulty breathing, insomnia, anorexia, constipation, diarrhea, and economic impact [43].

The EORTC-QLQ-C30 presents in most of the studies performed a good internal consistency (Cronbach α=0.7 for most of the scales). This questionnaire, based on a specific formula, obtains results on a scale from 0 to 100, where a higher score indicates a better quality of life. The scores for each question within each dimension (physical, emotional, and social functioning) are summed [44]. Within this questionnaire, there are specific modules that complement it for some types of cancer, for breast cancer they have created the EORTC QLQ-BR23 [44].

#### EORTC Quality of Life Questionnaire, QLQ-BR23

This questionnaire is a specific module for breast cancer that complements the previous questionnaire. Two main aspects are assessed here: functional scale (body image, sexuality, and concern for the future) and symptom scale (breast symptoms, arm, and side effects of treatment). It presents in most of the studies carried out a good internal consistency (Cronbach α=0.7) [44]. Like the general module, this questionnaire has a score from 0 to 100, where they are transformed according to a formula by specific dimensions.

### Ethical Considerations

In this study, clinical investigations involving medical devices are conducted on human participants. In order to safeguard the integrity, well-being, and privacy rights of the participants, the study is carried out in accordance with the guidelines set forth by the Declaration of Helsinki of the World Medical Association (64th General Assembly, Fortaleza, Brazil, October 2013), the Council of Europe Convention on Human Rights and Biomedicine, Good Clinical Practice standards, Royal Decree 1090/2015 of December 4, which regulates clinical trials with medicinal products, the Research Ethics Committees for Medicinal Products and the Spanish Registry of Clinical Studies, and Royal Decree 1591/2009 of October 16th, which regulates medical devices [45,46].

The study protocol will be submitted to the Bioethics Committee at the University Hospital of Torrecárdenas for review and approval in February 2025, during the preparatory phase. Ethical approval will be obtained before the initiation of any participant recruitment or data collection activities, in compliance with ethical standards. Recruitment is scheduled to begin in February 2025, contingent on receiving ethical approval. The ethical approval number will be provided in the final manuscript once it is obtained.

Before the study commences, explicit informed consent will be requested from participants via a digital form, clearly explaining the study’s objectives and participation details (Multimedia Appendix 1). Participants will have the ability to opt out at any stage without consequences. For any secondary data analyses, it will be confirmed that prior institutional review board–approved consent covers reuse without requiring additional consent. Compliance with Spanish Organic Law 3/2018 of December 5, 2018, on the Protection of Personal Data and the guarantee of digital rights [47], will also be ensured. Participant privacy will be rigorously protected, and all collected data will be anonymized or deidentified to prevent the disclosure of personal information. The data will be securely stored and used exclusively for this research project and any resulting publications. If any identifiable data is included in images or supplementary materials, explicit consent will be obtained and the necessary documentation will be submitted as supplementary files.

Participants will not receive any financial compensation for their participation in the study. However, they will be provided with detailed information about the study’s objectives, potential benefits, and their rights as participants to ensure transparency and fairness in the research process. These measures ensure that the study adheres to the highest ethical standards and prioritizes participant safety, confidentiality, and informed consent in compliance with national and international research ethical regulations.

### Intervention

The proposal will be carried out in the intervention group (group 1), while the control group (group 2) will undergo the conventional recommendations indicated for this type of patient.

A supervised training plan will be carried out for 12 weeks with a frequency of 3 sessions per week with a duration of 60 minutes, an ideal estimate according to the meta-analysis of Montaño-Rojas et al [48]. In first 2 weeks, the group exercises will be performed to familiarize the participants with the exercises and then each participant will perform them at home with a review every 2 weeks to assess the increase of the load.

The exercises and loads included in this treatment plan have been designed and modified based on previous clinical trials [39,49-51]. The training plan will work the upper limbs, lower limbs, and trunk. All sessions begin with a general warm-up, which will be previously instructed to the participants, in which the heart rate will be increased (Multimedia Appendix 2). After a 2-minute break, the specific block of each session will begin (Textbox 1 and Multimedia Appendix 2). All exercises will be performed with dumbbells, elastic bands, and a ball. We will consider the age of each participant, making minor adjustments to the initial exercise program as needed.

Three sets of all exercises will be performed with 10-12 repetitions at 50%-60% 1 MR (previously calculated for each participant in each of the exercises) with 1 minute of rest between sets. Finally, we will conclude with general stretching previously instructed (Multimedia Appendix 2). The control group will participate in a general education and wellness program designed to promote overall well-being and maintain a basic level of activity. This program, matched in duration to the experimental group, will include regular counseling sessions covering topics such as nutrition, stress management, sleep quality, and relapse prevention. In addition, participants will be encouraged to engage in low-impact physical activities, such as short walks and gentle mobility exercises. For the experimental group, the supervised exercise program aims to improve pain, physical function, and quality of life through a variety of carefully selected exercises tailored to each participant’s needs. These include stretching exercises, such as pectoral stretches for chest mobility and shoulder and arm stretch to enhance the range of motion and relieve tension. Strength training exercises using resistance bands or light weights will focus on improving upper limb and core strength to enhance posture and stability. Aerobic activities like walking or stationary cycling will be incorporated to boost cardiovascular endurance and mobility. Flexibility exercises, including range-of-motion activities, will help maintain and improve overall flexibility, while balance and coordination exercises will enhance stability and prevent falls. Muscle endurance will also be developed through lightweight or resistance band exercises. The program's design emphasizes a personalized approach, guided by physiotherapists or exercise specialists, to ensure safety and maximize benefits for patients with cancer.

Strength exercises included in the training plan.

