**Methods:**

This randomized, double-blind clinical trial will recruit 325 participants, divided into an intervention group receiving the exercise program and a control group receiving standard care recommendations. Outcome measures, including pain (assessed via the Brief Pain Inventory), physical function (Disability of the Arm, Shoulder, and Hand Questionnaire), and quality of life (European Organization for Research and Treatment of Cancer QLQ-C30 and European Organization for Research and Treatment of Cancer QLQ-BR23), will be evaluated at baseline, immediately post intervention, and 12 weeks post intervention. Statistical analysis will involve repeated measures of ANOVA and MANOVA to determine the significance of the intervention’s effects across time points.

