**Conclusions:**

Physical exercise is anticipated to play a significant role in alleviating pain, enhancing physical function, and improving the quality of life in female patients with cancer. This study will provide robust evidence to support the integration of supervised exercise into standard care protocols for this population.

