### Study Design

This study will be a single-blind, randomized clinical trial. To determine the efficacy of a therapeutic exercise program on the different dimensions of quality of life, physical function, and pain in patients with cancer. Once the participants have been recruited, they will be randomly assigned to 2 groups (intervention group and control group). Three assessments will be made: initial assessment, assessment after the end of the intervention, and assessment 12 weeks after the end of treatment. The intervention group will follow a 12-week therapeutic exercise plan, and the control group will follow the usual recommendations for this type of patient. After this last assessment, the participants in the control group will be offered the intervention. (Figure 1). Approval will be sought from the ethics committee of the University Hospital of Torrecárdenas.

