### Data Management and Analysis

Once all the measurements included in the measuring instruments section have been taken, they will be recorded and analyzed using SPSS (version 28.0; IBM Corp) [52].

The quantitative data of the sample will be described by number, mean, and SD.

A result is understood to be significant when *P*≤.05. In statistics, significance or internal consistency indicates that there is congruence between the different results obtained [53].

For the statistical analysis of the results of this test, 2 tests will be performed as follows.

Repeated measures ANOVA: This analysis allows us to evaluate whether the differences between the results of the same test in a participant are statistically significant. If so, it also determines what percentage of the effect is attributable to the intervention and not to other factors [53]. Two ANOVA analyses will be performed: one comparing the preintervention assessment with the postintervention assessment, and the other comparing the postintervention with the assessment 12 weeks later. This test will check if there is a significant improvement in the different measures of pain, physical function, and quality of life. Finally, the paired comparison table will tell us in which measurement periods the differences are found [53].ANOVA of differences: In this case, the differences between the results of the intervention group and the control group will be compared [53]. With the results obtained from this statistical analysis, it will be possible to verify whether the differences between groups in terms of pain, physical function, and quality of life are significant between the participants receiving the intervention and those belonging to the control group.MANOVA: To assess the overall effect of the intervention and determine whether the hypotheses can be accepted or refuted, the following hypotheses will be tested [53].

These statistical analyses described the significance between the test results of the same individual and the significance between the different results of both groups of the test that will be tested.

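### The control arm is labelled as standard, usual or conventional recommendations, but the only operational description gives it a duration-matched education and wellness program with regular counselling

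*Protocol article*

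**What the plan says.** Three places give the comparator a short label. The Methods paragraph of the Abstract has "a control group receiving standard care recommendations". Study Design says that "the control group will follow the usual recommendations for this type of patient". The first paragraph of Intervention says that "the control group (group 2) will undergo the conventional recommendations indicated for this type of patient".

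Further on in Intervention, after the exercise dose, the control condition is described again, this time with content: "The control group will participate in a general education and wellness program designed to promote overall well-being and maintain a basic level of activity". The next sentence adds: "This program, matched in duration to the experimental group, will include regular counseling sessions covering topics such as nutrition, stress management, sleep quality", and it also lists relapse prevention. A third sentence encourages light activity such as walking and gentle mobility work.

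The Hypothesis section defines controls only by their not receiving the exercise program. Under Data Management and Analysis, "the differences between the results of the intervention group and the control group will be compared" for pain, physical function and quality of life.

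**The concern.** The comparator is half of the treatment contrast. Following recommendations and taking part in a program with counselling sessions are different control conditions, and they answer different questions: what exercise adds to usual advice, or what exercise adds to an education and counselling program.

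The distinction bears on these outcomes. Pain, function and quality of life are measured largely by questionnaire. Some counselling topics also overlap with what the questionnaires cover: the QLQ-C30, as the article describes it, includes insomnia and emotional functioning, and controls are to be counselled on sleep quality and stress management. Controls given the program could therefore move on those scales in a way that controls given advice alone might not.

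At stake is the description of the result. A reader or meta-analyst who relies on the Abstract would classify this as a trial against standard care recommendations.

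**Working it through.** No figure in the plan depends on this point, so the check is a comparison of every description of the control arm.

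| Place | What controls receive | Kind of statement |
|---|---|---|
| Abstract, Methods | Standard care recommendations | Label |
| Hypothesis | Not the exercise program | Fits either version |
| Study Design | Usual recommendations | Label |
| Intervention, first paragraph | Conventional recommendations | Label |
| Intervention, after the exercise dose | Education and wellness program, matched in duration, with regular counselling | Operational description |

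1. **Does any text equate the label with the program?** No. The operational sentences do not mention recommendations or usual care, and the three labels do not mention a program.

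2. **Could the program simply be usual advice spelled out?** Usual advice exists whether or not a trial is running. A program whose duration is set to match the experimental arm is defined by reference to the trial. This holds whether duration means the 12 weeks or the length of sessions. So the program is more than the labels convey.

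3. **Which elements carry the disagreement?** The program itself, its matching to the other arm, and its regular counselling. The light-activity sentence could belong to usual advice, so it is not counted. The Hypothesis section is not counted either.

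4. **How many participants does it govern?** The Sample section gives 325 in total, and "Assignments will be randomized with a 1:1 ratio". 325 / 2 = 162.5, so 162 or 163 controls.

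5. **Can the gap between the two versions be sized?** No. The article gives no counselling frequency, so contact time cannot be computed. It does not describe usual care at the hospital, and it gives no expected effect under either comparator.

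**The case against.** The strongest reply is that this is ordinary drafting: a short label first, the content later in the same section. The exercise arm is treated the same way. On that reading staff have only one description to carry out, so delivery is not in doubt. The counselling topics are lifestyle advice of a kind that could be given as recommendations. The article does not say who runs the program or whether the hospital already offers it, and matched in duration may mean no more than the same 12 weeks. The source is also a condensed article.

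Much of this stands as an account of what will probably be delivered: the operational text is the likelier guide. It does not rescue the labels. If the program is what controls receive, three places describe the comparator as recommendations without saying that these take the form of a duration-matched program with counselling. Condensation explains missing detail, not affirmative statements that disagree.

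Three stronger readings are tempting, and the documents do not support them.

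- A reader might infer that the Abstract's conclusion is also wrong, where it says "This study will provide robust evidence to support the integration of supervised exercise into standard care protocols for this population". That sentence is about where exercise should be adopted, not what it was compared with. A benefit over an education program could still support adding exercise to standard care.
- A reader might infer a contact-matched attention control with a smaller expected effect, and hence a loss of power. No session frequency or contact time is given for controls, and the assumed effect size of 0.5 is not tied to either comparator.
- A reader might infer that the control condition was badly chosen. Either one is legitimate; the fault is that the text does not settle on one.

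**Conclusion.** The point holds as a disagreement between the comparator label and the control condition described for delivery. It should be fixed, but it is not a fatal flaw. That the texts disagree is clear from the wording. How far the two conditions differ in practice is uncertain, because local usual care is not described.

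The consequence lies in interpretation. Run as the operational text says, the trial would estimate exercise versus an education and counselling program while its Abstract announces a comparison with standard care recommendations. No sample size, test or other number in the plan changes. The conclusion rests on one assumption: that a program matched to the experimental arm is not identical to advice these patients already receive. If the hospital already provides exactly this program as usual care, a sentence saying so would resolve the point.

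**What to change.** Before the first randomisation, confirm one control condition and make the text agree.

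- **If it is the education and wellness program:** name it as the comparator in the Abstract's Methods paragraph, in Study Design and in the first paragraph of Intervention. Report the between-group comparison under Data Management and Analysis as exercise versus that program, not versus standard care recommendations alone.
- **If it is usual recommendations only:** delete the two Intervention sentences that set out the program and its counselling. The light-activity sentence can stay if that encouragement is part of usual advice.

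The Abstract's conclusion need not change in either case. The cost is rewording in three places or the deletion of two sentences, with no extra participants, visits or analyses. The only downside is that keeping the program narrows what the trial can conclude.
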